## Abstract

**Supplementary Information:**

The online version contains supplementary material available at https://doi.org/10.1186/s40359-026-04749-2.

Criminal-legal involvement is a salient yet frequently under-assessed risk factor for suicide. In 2019, 27.2% of suicide deaths in the United States (U.S.) occurred among individuals who had been incarcerated within the previous two years [1]. Results of a recent meta-analysis also suggest risk for suicide is more strongly associated with criminal-legal involvement than many other social determinants of health, including exposure to suicide mortality, firearm access, and occupational stress [2]. Risk for suicide is also particularly elevated among persons with co-occurring difficulties, such as mental health concerns or housing instability [3, 4]. Preventing suicide therefore requires addressing the criminal-legal involvement and co-occurring difficulties of at-risk persons. This manuscript describes an intervention to decrease criminogenic and suicide risk among U.S. military Veterans experiencing criminal-legal involvement (VCLI) and outlines a corresponding clinical trial to evaluate the efficacy of this intervention. Particular attention is paid to considerations around culture and clinical needs of the presenting population, suicide risk assessment and management, and treatment engagement strategies required in development and evaluation of interventions for individuals at concurrent risk for criminal-legal involvement and suicide.

## Veterans with criminal-legal involvement

VCLI are a high-risk, high-need population overrepresented in behavioral healthcare settings within the U.S. Department of Veterans Affairs (VA), a federal entity that provides healthcare, social services (e.g., housing support), benefits (e.g., financial compensation for service-related injuries), and funeral services to eligible military Veterans (VA; [5]. In 2023, the suicide rate for VCLI was approximately 145 per 100,000, over four times that of Veterans overall and over eight times that of civilian adults [6]. Results of a recent meta-analysis suggest 81% of VCLI experience a mental health condition and 69% experience a substance use disorder; rates of mood, trauma-related, and personality disorders appear particularly overrepresented in this population [7]. In comparison to Veterans without a history of criminal-legal involvement, VCLI are also more likely to engage in suicidal, violent, and otherwise aggressive behaviors and to experience homelessness, occupational instability, and poor community integration [8–11]. These challenges may contribute to difficulties with sustained service engagement by increasing transience, introducing demands for complex care coordination, and prompting crisis intervention that can interfere with care continuity (e.g., inpatient hospital stays).

To support VCLI, VA offers programming through Veterans Justice Programs (VJP) to connect Veterans with VA-based health care and case management services, including mental health and substance use disorder treatment, primary care, housing support, and other identified areas of need [12, 13]. Nevertheless, when any services are provided in isolation, they are likely insufficient in reducing risk for criminal-legal involvement and addressing the range of difficulties commonly faced by VCLIs [14, 15]. Forensic-oriented interventions that specifically target risk factors for criminal-legal involvement (e.g., antisocial attitudes and behaviors) are likely necessary. However, a survey of VJP specialists suggests numerous barriers to implementing such interventions, including patient perceptions of forensic programming as lengthy, intensive, and unappealing to internal motivations and provider biases against Veterans who engage in antisocial behaviors [16]. Consistent with this, recent efforts to implement and evaluate Moral Reconation Therapy [17] – an evidence-based intervention to decrease criminogenic thinking – in VA settings faced notable difficulties with patient engagement and staff adoption [18, 19].

Considering these barriers, effective clinical interventions for VCLI will likely require programming to be brief, appealing to VCLI’s internal motivations, and relevant to behavioral health providers. Such intervention would also need to balance efforts across a range of treatment targets, including risk for criminal-legal involvement, risk for suicide, behavioral health concerns, and other forms of psychosocial stress (e.g., housing instability, financial insecurity, etc.).

## Dialectical behavior therapy for justice-involved veterans

Dialectical Behavior Therapy for Justice-Involved Veterans (DBT-J; [20] was developed with consideration of the presenting needs of VCLI and identified barriers to implementing forensic-oriented programming in VA settings. It combines elements from leading treatment modalities in offender rehabilitation (Risk-Need-Responsivity Model [RNR]; [21], suicide and mental health (Dialectical Behavior Therapy [DBT]; [22], and forensic case management (Socioenvironmental Disadvantage Model [SDM]; [14] to offer an integrative, manualized approach to simultaneously address VCLI’s criminogenic, behavioral health, and case management needs. The structure and content of DBT-J was also informed by feedback from experts in intervention development for persons at risk for suicide and criminal-legal involvement, VJP specialists, and VCLI themselves.

### Treatment structure

DBT-J provides 1–1.5 h of intervention per week for 16 weeks through group therapy, individual case management, measurement-based care, and provider participation in a specialized consultation team. The DBT-J program structure is consistent with recent research suggesting DBT-based interventions that are abbreviated and/or comprise only group therapy, case management, and consultation team typically yield outcomes comparable to the 12-month, comprehensive DBT-model [23, 24], even in the treatment of legally-involved persons [25]. The combination of group therapy and case management interventions allows DBT-J to be both standardized and individualized to each Veteran’s unique needs. All elements of DBT-J are provided via telehealth, thereby facilitating sustained engagement even while navigating difficult life circumstances, such as transportation barriers, housing instability, and admission to residential treatment.

#### Group therapy

The group therapy component of DBT-J promotes development, strengthening, and generalization of behavioral skills to effectively manage emotions, behaviors, and relationships underlying criminogenic risk and behavioral health difficulties. This component progresses through six modules – observing limits, foundational mindfulness, emotion regulation, goal directedness, interpersonal relationships, and relapse prevention. See Table 1. The included skills draw from RNR- and DBT-based interventions to maximize relevance of group content to VCLI needs. For example, given previous research implicating poor emotion processing and regulation – particularly in response to trauma – as underlying offending behavior [26, 27], the emotion regulation module draws heavily from DBT to teach foundational skills in understanding, processing, and managing emotional reactions and behavior. Further, given common difficulties in empathy and interpersonal connection among legally-involved persons [28, 29], the interpersonal relationships module includes a *mindfulness of others* skill through which participants learn step-by-step strategies for validation and building emotional closeness with others. Each group session includes: (a) completion of a brief mindfulness exercise (5 min); (b) review of homework from the previous week (20 min); (c) introduction and in-session practice of a new skill (30 min); and (d) assigning of between-session homework to promote generalization of skills to real-life experiences (5 min).

**Table 1 Tab1:** Correspondence between DBT-J content and treatment targets

Skills Group Schedule	Corresponding Treatment Target												
	Criminogenic Needs							Behavioral Health Needs					Socioenvironmental Needs
	Antisocial Personality	Antisocial Attitudes	Antisocial Peers	Substance Use	Educational / Vocational Difficulties	Family Difficulties	Lack of Prosocial Activities	Suicide Risk	Mood Disruption	Emotion Dysregulation	Interpersonal Difficulty	Executive Functioning Disruption	Case Management Difficulties
Observing Limits	X	X	X	X		X					X		
Mindfulness	X			X		X		X	X	X	X	X	
Dialectical Thinking	X			X		X		X	X	X	X	X	
Mindfulness of Self				X				X	X	X			
Emotional Schemas		X		X				X	X	X			
Thinking Errors	X	X		X				X	X	X			
Check the Facts & Opposite Action				X				X	X	X			
Self-Soothe & TIPP								X	X	X			
Values Clarification	X	X	X	X	X	X	X			X	X	X	X
Mindfulness of Goals	X		X	X	X	X	X			X	X	X	X
Problem Solving	X				X	X	X	X		X	X	X	X
Distress Tolerance & Radical Acceptance	X			X	X			X	X	X			X
Assertiveness	X		X			X					X		X
Mindfulness of Others	X	X	X			X					X		
Making Prosocial Relationships			X								X		
Relapse Prevention	X			X			X	X	X				

#### Case management

Case management sessions, led by the same provider leading the group therapy portion of DBT-J, are held every other week for up to 30 min to assist in coordinating connection to and care between the treatment team, legal services, and social services within the VA system and/or VCLI’s community. For example, for VCLI with active substance use, sessions may facilitate connection to local 12-step programs to support efforts toward sobriety. For VCLI facing financial difficulties, sessions may include referral to VA benefits advisors. Where possible, providers coach clients through applying skills learned in group therapy sessions (e.g., problem solving) to resolve case-management difficulties. Motivational interviewing strategies are also used throughout these sessions to promote sustained connection to care. Informed by SDM, case management is tailored to the client’s unique needs and balances foci on resolving factors contributing to criminogenic risk (e.g., substance use) with those prioritized by the Veteran (e.g., financial instability).

#### Assessment

Periodic assessments throughout the course of DBT-J participation allow for measurement-based care, consistently shown to improve treatment effectiveness [30]. Assessments include, for example, previously validated measures of criminogenic risk (e.g., The Level of Service / Case Management Inventory; [31], psychosocial functioning (Inventory of Psychosocial Functioning; [32], and suicide risk (e.g., Beck Scale for Suicidal Ideation; [33]. Assessment results are shared with participating VCLI during individual case management sessions, documented in Veterans’ electronic medical records, and used to guide collaborative treatment and case management planning.

#### Consultation team

The final treatment component, provider involvement in a weekly consultation team meeting, is considered standard for traditional DBT programs [22]. These meetings are attended by providers only; VCLI do not attend or participate in consultation team meetings. Consultation team meetings provide a forum for providers to troubleshoot barriers to care, support one another, promote adherence to the treatment model, and protect against provider burnout [34].

### Early evidence of efficacy

Two small scale clinical trials have evaluated the feasibility, acceptability, and preliminary efficacy of DBT-J [20, 35]. Across both studies, results suggested DBT-J is feasible and acceptable, with strong attendance, high engagement, and positive qualitative feedback about the program from VCLIs and referring providers alike. Participants reflected the great heterogeneity of the broader VCLI population. Collapsing across both studies, nearly half of participants had a personality disorder, two-thirds had a current substance use disorder, and over three-quarters had another form of mental health condition (i.e., mood, psychotic, anxiety, trauma-related, and/or intermittent explosive disorder). Consistent with RNR principles suggesting highest-intensity services should be reserved for persons at higher risk for criminogenic behavior [21], collapsing across trials, 82% were at moderate or high risk of criminal behavior upon admission, and none were at high risk upon program completion [20, 35].

Qualitative feedback from the first of these trials suggested the program’s relatively brief duration and balanced focus on criminogenic and non-criminogenic needs appealed to VCLI’s internal motivations and encouraged strong engagement, whereas it’s similarity to traditional DBT skills groups and partial focus on behavioral health appealed to VA providers, treatment courts, and other potential referral sources [20]. In the second trial, those who completed DBT-J experienced statistically significant improvements in risk for criminal behavior from pre- to post-treatment, and these gains were maintained at one-month follow-up [35].

Participants in these studies provided pivotal feedback to increase the cultural responsiveness of DBT-J for a U.S. military Veteran population. For example, VCLI offered culturally relevant metaphors to support skill presentation (e.g., drawing parallels between emotion mind-reasonable mind distinctions and off duty-on duty mindsets during military service), highlighted the potential contributions of prior service to current experiences (e.g., military culture as a potential contributor to emotional schemas and thinking habits), and suggested adaptations to the clinical style of group leaders to better mirror interpersonal styles common within military contexts (e.g., increased use of irreverence).

### DBT-J and suicide risk

The structure and content of DBT-J directly targets overlapping risk factors for antisocial behavior and suicide by: (a) building and strengthening behavioral skills for observing limits, mindfulness, emotion regulation, goal directedness, interpersonal effectiveness, and relapse prevention; and (b) facilitating connection to services and resources that reinforce use of adaptive skills. In early DBT-J trials, one-third of participating Veterans had a history of attempting suicide, and one-third were experiencing suicidal ideation upon program admission [20, 35]. Although analyses were underpowered to detect statistically significant effects, Veterans who completed the program experienced, on average, moderately sized (*d* = 0.30–0.88) improvements in multiple suicide risk factors across the course of treatment, including substance use, psychological distress, and quality of life [35].

DBT-J providers utilize a formal suicide risk assessment and management protocol designed for Veteran samples and VA contexts [36] to facilitate ongoing risk monitoring and efficient, therapeutic responses to acute changes in VCLI suicide risk. Comprehensive suicide risk assessments prior to program entry provide an initial conceptualization of VCLI acute and chronic risk for suicide (i.e., immediate risk and propensity toward increases in immediate risk, respectively). Ongoing monitoring of risk and protective factors is then used throughout the course of the VCLI’s participation in DBT-J to guide suicide risk assessment and management. Notable changes in risk and/or protective factors (e.g., increase in psychosocial stress, decrease in social support) prompt more structured suicide risk assessment and management strategies as necessary to promote VCLI safety. Various VA-based supports, such as those offered by the Veterans Crisis Line, VA Suicide Prevention Coordinators, and other behavioral health providers, are also integrated into suicide risk management efforts to promote effective, sustained risk mitigation.

### DBT-J engagement strategies

Wide ranging psychosocial needs, relational trauma histories, difficulties with interpersonal attachment, and general distrust toward social systems often pose barriers to effective treatment engagement for persons with criminal-legal involvement [29, 37–39]. DBT-J therefore employs various targeted engagement strategies to promote effective, sustained participation in DBT-J programming. A trauma-informed approach emphasizes participant choice while simultaneously acknowledging that the VCLI’s experience of navigating systems has limited their choices, consistent with dialectical strategies used in DBT [22]. Many VCLI may feel entrapped or otherwise devoid of choice throughout their navigation of the criminal-legal system. In contrast to this dynamic, DBT-J is presented as completely voluntary, even if being completed as part of a court-issued treatment mandate. VCLI are encouraged to embrace their freedom of choice when deciding whether to enroll in the DBT-J program and whether to continue participation. Should VCLI decide to discontinue participation, they are provided the option of changing their decision until their fourth consecutive group absence, similar to standard DBT.

DBT-J providers also work to tie participation and engagement to VCLI’s pre-existing goals, such as reunification with family, achieving financial independence, and moving past their criminal-legal difficulties. In doing so, VCLI are encouraged to view DBT-J participation as a step in their journey toward building the lives they want for themselves. Correspondingly, providers demonstrate personal investment in VCLI goals, progress, and accomplishments by tying introduced skills and program content to VCLI’s previously expressed goals (e.g., “Could we role play how you might practice this skill during your upcoming court appearance?), checking in about progress toward goals (e.g., “How did that court appearance go last week?”), and celebrating progress and achievements (e.g., “I’m so impressed how you were able to use skills to keep your composure during court last week!”). VCLI are also encouraged to connect with DBT-J providers between session to share progress, achievements, and other updates.

Targeted considerations also encourage appropriate engagement over a virtual platform. Many VCLI may struggle to engage in effective interpersonal behaviors due to several factors, including emotional reactivity, judgmental thinking patterns, interpersonal hostility, and deficits in empathy and impulse control [28, 40, 41]. To promote effective interpersonal behavior, particularly within group-based treatment settings, the first skill introduced within the group therapy portion of DBT-J is “observing limits” – a skill focused on respecting the limits of others and avoiding values-inconsistent behaviors. Where necessary, DBT-J providers also employ contingency management and shaping-based strategies to encourage effective engagement. For example, providers may limit the speaking time of participants when they engage in interpersonally ineffective behaviors (e.g., interrupting others, speaking out of turn) and extend speaking time when participants engage in interpersonally effective behaviors (e.g., staying on topic). Similarly, providers may initially encourage low-engagement participants to join sessions with video camera off to promote consistent attendance before then encouraging attendance with camera on.

Telehealth delivery may present a barrier to engagement for some VCLI, particularly those experiencing financial instability and those with less comfort using technology. To mitigate these barriers, DBT-J providers and staff offer, as needed, formal orientation to the virtual delivery platform, technological troubleshooting assistance, and referral to the VA Digital Device Program, which provides no-cost, internet enabled tablets for accessing telehealth-based services.

DBT-J providers and staff also consistently engage in “friendly harassment” – frequent contact with VCLI both in and out of session. On days of scheduled sessions or assessments, VCLI receive multiple reminders of the impending session using multiple modalities, such as email, phone, and text message. Targeted outreach and shaping strategies are also used with VCLI running late to sessions to promote attendance.

### Need for continued research

Research to date attests to the promise of DBT-J as an intervention for VCLIs. However, it has relied on pre-post designs with modest sample sizes, making it unclear whether observed effects stemmed from participation in DBT-J treatment or extraneous variables, such as the passage of time or receipt of outside services. Continued research using a larger sample and comparison against a control condition is therefore needed to evaluate the potential efficacy of DBT-J.

Further research is also needed to clarify differences in DBT-J treatment response across VCLI subgroups, such as those with severe mental health diagnoses, active substance use disorders, violent offense histories, and/or elevated acute risk for suicide. Such difficulties are commonly considered exclusion criteria for behavioral health programs and many psychotherapy trials, including those provided to justice-involved persons [42–45]. The protocol outlined in the remainder of this manuscript is being used to assess the efficacy of DBT-J and address these limitations of prior research on this intervention.

## Randomized clinical trial

A multisite randomized Stage III clinical trial will be conducted to assess the efficacy of DBT-J. A total of 200 Veterans will be recruited across three regions in the U.S. (VA VISNs 2, 19, and 21) over three years (2024–2026; anticipated date of recruitment completion, June 30, 2026). Random assignment, stratified by region and generated using an electronic random number generator, will be used to assign participating Veterans to DBT-J or a supportive group therapy condition. Assignment will be completed immediately after enrollment and available only to the PI and individuals involved in intervention delivery; assignment is masked from individuals involved in assessment completion. Veterans will receive 16 weeks of assigned intervention followed by a 36-week observation period. To inform evaluations of treatment efficacy, participants will also complete assessments in 8-week intervals during the intervention period beginning at baseline and 12-week intervals during the follow-up period (6 times total). See Table 2. All protocols were developed in accordance with the Declaration of Helsinki and have been approved by the VA Central Institutional Review Board; protocols and analysis plans are pre-registered through clinicaltrials.gov (NCT05974553, registered July 26, 2023). All participants will provide informed consent prior to participation. To preserve participant confidentiality, individual participant data will not be shared with anyone outside of the immediate research team.

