### Data analysis plan

Analyses will employ an alpha of 0.05, use two-tailed tests, and be completed using SPSS and/or the R Computing Environment. Preliminary analyses will include computing descriptive statistics and inspecting data to determine whether data transformations are needed, statistical assumptions are met, and psychometric properties of each scale are sound. Multiple imputation will be used for transient missing data. Because participants who dropout of the protocol may be qualitatively distinct from protocol completers (e.g., due to differences in motivation, legal requirements, etc.), analyses will also include a sensitivity analysis by comparing the full “intent-to-treat” sample against protocol completers. Potential confounders, including duration of outside treatment services received during the intervention period, will be compared across conditions and included as covariates in subsequent analyses if significantly related to study outcomes.

Primary and secondary analyses will be investigated using analyses of covariance to compare participants in the DBT-J and supportive group conditions on primary and secondary continuous treatment targets at post-treatment after controlling for baseline scores. Poisson regression with robust error variance will similarly be used to compare DBT-J and comparison conditions on dichotomous secondary treatment targets (suicide attempt during study period and criminal recidivism during study period). The DBT-J condition will be considered superior to the supportive group condition if participants in the DBT-J condition demonstrate statistically superior scores on either primary treatment target at post-treatment. The DBT-J intervention will be considered efficacious if results suggest (a) superiority to the supportive group condition and (b) clinically significant change in primary efficacy outcomes from baseline to post-treatment among DBT-J participants [67].

To support exploratory analyses comparing efficacy of DBT-J programming across VCLI subgroups, DBT-J participants will be coded according to most recent offense type (violent or nonviolent), presence of a substance use disorder, and presence of a severe mental illness (i.e., mood or psychotic disorder). Multivariate analyses of covariance will be used with subgroup membership included as predictor variables, LS/CMI and IPF post-treatment scores included as dependent variables, and LS/CMI and IPF baseline scores included as covariates.

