#### Justification of sample size

A priori power analysis was used to determine an appropriate sample size to support primary aim analyses. Informed by results of previously collected pilot data [20, 35], we anticipated at least a moderately-sized difference across conditions in primary efficacy outcomes at post-treatment. Power analysis results suggested at least 80 participants per condition (160 total) are needed to achieve 80% power to reject the null hypothesis of equal means when the population mean difference is *d* = 0.50 and α = 0.025 (to adjust for multiple comparisons). After adjusting for an anticipated dropout rate of 20%, 100 participants per condition (200 total) are required to achieve necessary statistical power.

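### Region stratifies the randomisation but is not a guaranteed term in the primary ANCOVA; if region is prognostic, some precision is lost

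*Protocol article*

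**What the plan says.** Under Randomized clinical trial, the protocol article states: "A total of 200 Veterans will be recruited across three regions in the U.S. (VA VISNs 2, 19, and 21)". It specifies "Random assignment, stratified by region and generated using an electronic random number generator". Region is therefore a design factor with three levels. The article does not say whether assignment within a region is blocked.

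Under Data analysis plan, the model is given as "Primary and secondary analyses will be investigated using analyses of covariance to compare participants in the DBT-J and supportive group conditions", with the comparison made "at post-treatment after controlling for baseline scores". Region does not appear there. A separate sentence allows potential confounders to be "included as covariates in subsequent analyses if significantly related to study outcomes"; the one example it gives is the duration of outside services. The dichotomous secondary outcomes are assigned a robust-variance Poisson regression, with no covariate list of their own.

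Two significance levels appear. Data analysis plan says "Analyses will employ an alpha of 0.05, use two-tailed tests"; Justification of sample size uses "α = 0.025 (to adjust for multiple comparisons)".

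**The concern.** A factor that restricts the randomisation would normally be carried into the analysis. Suppose region predicts outcome and the arms are balanced within each region. The treatment estimate is then free of between-region variation, but a model without region still counts that variation in its residual variance. The reported standard error exceeds the true spread of the estimate, intervals are wider than they need to be, and the test rejects less often than its nominal level.

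The second issue is pre-specification. As written, region's only way into the model is a significance test on the trial's own outcomes. It could be in the model for LS/CMI and absent for IPF, or the reverse. Superiority is declared on a win on either of these two, so naming region in advance removes one data-dependent choice from that decision.

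**Working it through.** **The plan's own sample size.** Inputs from Justification of sample size: d = 0.50, alpha 0.025 (taken as two-sided), power 80%, 20% dropout.

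- Normal approximation: n per arm = 2(z₀.₉₈₇₅ + z₀.₈₀)²/d² = 2(2.2414 + 0.8416)²/0.25 = 76.04, so 77.
- Exact noncentral t: 78 per arm (power 0.804). At the stated 80 per arm, power is 0.815 (0.821 by the normal approximation).
- Dropout: 80/(1 − 0.20) = 100 per arm, 200 in total.

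The stated figures reproduce, and they assume no gain from adjusting for region.

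**Effect of leaving region out, with balance within region.** Let R² be the share of baseline-adjusted outcome variance explained by region. The documents give no value, so 0 to 0.10 is an assumed range. The calculation takes 80 per arm, d = 0.50 on the baseline-adjusted scale, and z = 2.2414 for alpha 0.025.

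- Ratio of reported to true standard error: 1/√(1 − R²).
- True two-sided alpha: 2{1 − Φ(z/√(1 − R²))}.
- Power without region: Φ((0.5√40 − z)/√(1 − R²)).
- Power with region: Φ(0.5√40/√(1 − R²) − z).

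For example, at R² = 0.05 the ratio is 1/√0.95 = 1.026, and true alpha is 2{1 − Φ(2.2414 × 1.026)} = 0.0215.

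| R² | SE ratio | True alpha (nominal 0.025) | True alpha (nominal 0.05) | Power without region | Power with region |
|---|---|---|---|---|---|
| 0 | 1.000 | 0.0250 | 0.0500 | 0.8214 | 0.8214 |
| 0.02 | 1.010 | 0.0236 | 0.0477 | 0.8239 | 0.8297 |
| 0.05 | 1.026 | 0.0215 | 0.0443 | 0.8276 | 0.8421 |
| 0.10 | 1.054 | 0.0181 | 0.0388 | 0.8341 | 0.8626 |

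The power differences are 0.58, 1.45 and 2.85 percentage points at R² of 0.02, 0.05 and 0.10.

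**Simulation, with and without forced balance.** There were 5,000 trials per setting, with 160 participants split 56/52/52 over three regions and a baseline coefficient of 0.5. Results at R² = 0.10 and alpha 0.025:

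| Assignment within region | Model | Mean reported SE | Actual SD of estimate | Type I error | Power |
|---|---|---|---|---|---|
| Blocks of four | without region | 0.158 | 0.152 | 0.018 | 0.827 |
| Blocks of four | with region | 0.150 | 0.152 | 0.026 | 0.858 |
| Simple | without region | 0.159 | 0.159 | 0.025 | 0.808 |
| Simple | with region | 0.152 | 0.151 | 0.026 | 0.839 |

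The Monte Carlo error on a type I rate near 0.025 is √(0.025 × 0.975/5000) = 0.002. Under blocking the test without region is conservative. Under simple randomisation its standard error is right for its own estimate, but larger than the adjusted one.

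**Cost of adjusting.** Residual degrees of freedom go from 160 − 3 = 157 to 160 − 5 = 155.

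**The case against.** The strongest reply is that this is an article, that the analysis plan is pre-registered and not shown, and that a full covariate list may sit there. Nothing in the article excludes region. That is fair as far as it goes. But the article names the model, its covariate and the rule for adding others, and that rule makes a design factor conditional on significance. The point is about what is stated.

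A reader might infer that the primary model adjusts for the baseline score and nothing else. The text does not say so: the screen could admit region.

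A reader might also infer that the trial's intervals will be too wide. That needs region to be prognostic beyond the baseline score, and balance within region. The documents establish neither. Baseline LS/CMI or IPF may already absorb much stable regional difference. The net direction is also open. Both arms meet in closed groups of at most 8, and the described model has no group term. With √(1 + 7 × ICC) and an assumed ICC of 0.01, 0.05 or 0.10, the true standard error would be about 3%, 16% or 30% larger, which could outweigh the region effect. Clustering is a separate matter and gives no reason to omit region, but it rules out a claim about overall interval width.

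Finally, the formulas above are for linear models and give no magnitude for the Poisson outcomes. Suicide attempt may be sparse, and a region with no events would make its coefficient inestimable. This objection stands and limits the fix.

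**Conclusion.** The point holds in a limited form. Region is a stratification factor, it is not a named term in the primary ANCOVA, and its only route in is a significance screen. If region is prognostic after baseline adjustment, omitting it loses efficiency. If assignment is also balanced within region, the reported standard error is 1.0% to 5.4% too large and the test mildly conservative over an assumed R² of 0.02 to 0.10. If region is not prognostic, the effect is nil.

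Two stronger conclusions are not supported. One is that the benefit of stratifying is thrown away. Under balance the estimate itself is still more precise, and power without region rises from 0.821 to 0.834 as R² goes from 0 to 0.10; what is missed is the further gain to 0.863. The other is that the trial is underpowered as a result. The 80 per arm was set without any gain from region, so the stated 80% is unaffected by this omission, and omitting region does not inflate type I error. This is an inexpensive improvement and a gain in pre-specification; it does not repair a validity failure.

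**What to change.** State in the Data analysis plan, before outcomes are examined by arm, that region (three levels, fixed effect) is included with the baseline score in the ANCOVAs for LS/CMI, IPF and the continuous secondary outcomes, whatever its significance. State also that the covariate screen does not decide on region. For the Poisson models of suicide attempt and recidivism, include region only where event counts allow its coefficients to be estimated, and fix in advance what is done otherwise. The cost is a sentence or two in the plan and 2 degrees of freedom out of 157 in each ANCOVA. Sample size, assignment and data collection do not change.
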